#### PrEP technical assistance

The project conducts health care provider training, as noted above, and then ongoing on-site and remote mentorship. Technical advisors are project staff with expertise in PrEP research and clinical delivery. Each technical advisor oversees up to four clinics and conducts bi-monthly visits to each clinic to coach and mentor the health care providers and observe and document PrEP implementation processes, with a specific focus on processes that are effective or not and aspects of delivery that are changing with time. Using rapid-cycle analysis approaches, technical advisors make summary reports at the end of each clinic visit highlighting what changed, why it changed, who initiated the changes, and outcome of any changes instituted. Key emerging themes that impact PrEP delivery processes are quickly fed back to the facility for possible actions. Best practices for demand creation, clinical PrEP provision, and retention strategies are discussed with and shared across clinics for possible adoption. Detailed clinic-level reports are generated at baseline and 6-monthly to triangulate delivery processes with core components focused on changes in demand creation strategies, clinical PrEP provision, retention strategies, workforce and infrastructure, and monitoring and evaluation.

#### Data abstraction

Clinical records and program data are documented on standardized PrEP delivery MOH monitoring and evaluation systems. Dedicated project staff abstract program data (e.g., number of PrEP initiations, number of ART initiations) and individual clinical records. Individual data is used to characterize PrEP initiation, HIV risk profiles of PrEP initiators, self-reported adherence, retention, HIV infection, and side effects.

#### Evaluation of PrEP adherence

Adherence is essential for PrEP efficacy [22, 30]. At a subset of randomly selected visits (up to 10%), blood samples are collected from individuals taking PrEP and from possible seroconverters to test tenofovir levels as an objective measure of PrEP adherence. Additional evaluation of PrEP use includes pharmacy refill records (i.e., picking up each new PrEP supply) and self-report (e.g., self-rating, captured on the PrEP delivery tool). The goal is to understand both execution (i.e., adherence while used) and persistence (i.e., duration of use).

#### Qualitative interviews and exit surveys to understand delivery

Qualitative interviews are prospectively conducted to rigorously understand delivery, at the level of providers, organization (i.e., clinic), and users. Provider interviews with MOH staff at clinics (nurses, counselors, clinicians, clinic managers) focus on operational delivery to understand acceptance, barriers, facilitators, and opportunities for efficiency. After each interview, short debriefing reports are used to identify emerging themes that affect implementation and those are quickly fed back to clinics prior to formal qualitative analysis. Patient interviews also focus on delivery (e.g., waiting times, visit schedule, visiting HIV treatment centers, confidence in the health system, and community impressions of PrEP), structural (e.g., gender roles), individual (e.g., fertility desire), and dyadic (e.g., sexual negotiation skills, trust, power) factors that may influence PrEP implementation and use. Additional complementary exit surveys with a subset of patients focus on user experiences and satisfaction.4.*Economic evaluation*: Estimating program impact and cost is necessary to inform public health decision-makers when deciding on HIV treatment and prevention policies and resource allocation. Time and motion studies to follow patients through each PrEP service delivery point are conducted to characterize service delivery models, including appropriate personnel, task shifting, and costs. Program cost for delivery, time spent to deliver PrEP, laboratory costs, and retention activities (e.g., duration and cost of phone calls for appointment reminders) are documented. We also estimate the financial and opportunity cost to PrEP recipients of transportation and time spent at the clinic in exit surveys and time and motion studies.5.*Stakeholder engagement*: The project conducts relevant stakeholder engagement activities to facilitate buy-in and ensure PrEP delivery continues to scale up at the national level. The project team is part of the Kenya national PrEP Technical Working Group (TWG, which is charged with implementing PrEP for all at-risk populations nationwide) and uses this platform to offer guidance and technical support needed to deliver PrEP at scale on a national level. The project regularly conducts stakeholder meetings attended by representatives from the MOH, NASCOP, National AIDS Control Council, county government officials, other PrEP-implementing partners, clinic managers, and providers from all implementing clinics to review progress.

### Outcome measures and data sources

Key quantitative program implementation outcomes will include (a) Reach, defined as the number of at-risk persons initiating PrEP; (b) Effectiveness, defined as the number of HIV-uninfected on PrEP partners staying HIV-uninfected and adherence to PrEP as measured by tenofovir levels in DBS; and (c) Adoption, measured by PrEP continuation, number of serodiscordant couples newly identified through couples HIV testing. HIV risk profiles of PrEP initiators will be characterized using a validated risk score for HIV-serodiscordant couples [31], which we will use to further predict HIV incidence in the absence of intervention [14]. Monitoring and evaluation will measure patient, provider, and clinic level factors influencing delivery including clinic innovations, adaptations, barriers, and facilitators of PrEP implementation and opportunities for efficiency.

The project uses multiple data sources (Table 2) that will robustly synthesize and triangulate PrEP delivery processes to identify contextually relevant strategies for successful implementation, as well as practical difficulties in adoption, integration, and maintenance to inform wider implementation.

**Table 2 Tab2:** Data sources

Data source	Description	Purpose
Data abstraction	▪ Data abstracted from clinical delivery tools	▪ Define who is initiating PrEP and whether persons are appropriately put on PrEP
Technical assistance	▪ TA reports prepared at baseline and 6-monthly	▪Document details of the process of adoption and integration of PrEP delivery and track changes in PrEP implementation processes. ▪ Rapid cycle analysis to convey to facilities for quality improvement
Qualitative interviews: user and provider	▪ Purposefully sampled patient and key informants involved in the delivery	▪ Gain deep understanding of process of adoption and integration of PrEP delivery and track changes in PrEP implementation processes.
Time and motion studies	▪ Primary data collection	▪ Economic evaluation
Exit interviews	▪ Random on spot user structured surveys at the end of clinic visit	▪ User experiences and satisfaction
Random blood draw	▪ Dried blood spots collected at ~ 10% visits on persons using PrEP	▪ Objective assessment of PrEP adherence (tenofovir levels), resistance surveillance
Observation	▪ Informal	▪ Track changes in PrEP implementation processes.

### Data management and confidentiality

All abstracted health and patient data are handled in a secure and confidential way through adherence to institutional policies and procedures for securely storing, maintaining, and updating health record information. All health records and patient data are securely stored on password-protected and encrypted servers, and these data will not be released externally except under specific data-sharing agreements. All study results will be presented in aggregate, and no individual patient or provider will be identifiable.

### Analysis

#### Quantitative data

The primary outcome will be the number of at-risk persons initiated on PrEP (Reach). The number initiated on PrEP during baseline period (i.e., pre-implementation period) will be compared with that across the implementation observation periods (exposed or intervention period). Generalized linear mixed models, to estimate the primary intervention effect where both differences observed within steps (between randomized clinics) and changes observed within each clinic as it implements the intervention (within clusters), contribute information. A random effect for each clinic, a fixed effect for each time step, and the fixed intervention effect will be fitted for each time period. Categorical variables will be detailed in tables, and continuous measures will be summarized using means and standard deviations or medians and ranges, as appropriate. *T* tests will be used to detect differences in mean levels of continuous variables and chi-square tests for dichotomous variables.

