### Randomization

Beginning February 2017, we implemented a stepped-wedge trial design to randomly assign 24 HIV care clinics to scaled implementation of PrEP integrated in HIV clinics for couples. During the project pre-implementation period, PrEP was sanctioned as part of  standard of care by the Kenya national guidelines but there were no systematic approaches in place for implementation in clinical settings. The project intervention is to be a catalytic force to integrate PrEP delivery in public HIV clinics nationally and the intervention package includes staff training, clinic streamlined access to PrEP commodity from Kenya Medical Supply Authority (KEMSA), and ongoing PrEP technical assistance. Prior to randomization, the 24 clinics were stratified by region (12 Central, 12 Western), and each clinic was randomized to the order in which it would start implementing PrEP delivery. The randomization process was conducted at a public event attended by national and county health representatives. Facility leadership picked the order of initiation from an opaque bag containing numbered balls labeled from 1 to 12. Following randomization, the implementation was rolled out in groups of two to four clinics (Fig. 2). Program indicators to measure number of serodiscordant couples newly identified through couples HIV testing, number of HIV-uninfected individuals initiating PrEP, and number of HIV-infected individuals newly initiating ART are obtained monthly from all participating clinics starting 1 month prior to the project initiation.

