### Sample size

Using 24 clinics with a baseline period, two to four clinics implementing at each step, and 50 at-risk HIV-uninfected persons initiating PrEP per clinic every 6 months (200 couples on average per site overall, 4800 total), the trial is estimated to have > 90% power to detect a minimum 10% difference in the number of at-risk HIV-uninfected individuals initiating PrEP (defined below as Reach) after implementing the intervention, with a two-sided alpha of 0.05. This difference was conservatively chosen, recognizing that as interventions move to scale their impact is often diminished (a “voltage drop” along successive steps of an implementation cascade [20]).

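### The t and chi-square tests named for other comparisons make no allowance for clinic, so person-level p-values across clinics, regions, steps or periods can be materially too small

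*Protocol article*

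**What the plan says.** All of this is in the protocol article.

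- **Primary outcome (Quantitative data).** "The primary outcome will be the number of at-risk persons initiated on PrEP (Reach"). It is analysed by a generalized linear mixed model with "A random effect for each clinic, a fixed effect for each time step, and the fixed intervention effect".
- **Other variables (same section).** After a sentence on descriptive summaries, the article says that t "tests will be used to detect differences in mean levels of continuous variables and chi-square tests for dichotomous variables". It does not name the variables, the groups or the unit of analysis. It attaches no clinic effect, robust variance, clinic-level summary or time effect to these tests.
- **Person-level data (Data abstraction).** "Individual data is used to characterize PrEP initiation, HIV risk profiles of PrEP initiators, self-reported adherence, retention, HIV infection, and side effects".
- **Clusters (Randomization).** "the 24 clinics were stratified by region (12 Central, 12 Western").
- **Size (Sample size).** "200 couples on average per site overall, 4800 total", built on "50 at-risk HIV-uninfected persons initiating PrEP per clinic every 6 months", "with a two-sided alpha of 0.05".

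No ICC is given anywhere in the article.

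**The concern.** A two-sample t test or a chi-square test takes its standard error from the number of persons, as if each contributed independent information. People attending the same clinic share staff, demand creation and retention practice, and local risk. When the groups compared are made up of different clinics, as with region, step or a clinic feature, this shared variation goes straight into the difference between groups, but not into the test's standard error. A comparison between periods in a stepped wedge is partly of the same kind, because clinics contribute unequally to baseline and implementation. It also mixes any calendar trend with the intervention. A trend is plausible here: the Context section puts the national PrEP launch in May 2017, after the project's activation in February 2017, and says that rollout was expanding.

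The article recognises both problems for Reach and models them. The tests that it names for everything else carry neither protection. At stake is whether secondary differences, for example in continuation or risk profile between regions, are reported with more certainty than 24 clinics can give.

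**Working it through.** **1. The plan's own figures.** 24 clinics × 200 = 4,800, as stated. 50 initiations per 6 months × 4 = 200 per clinic, which implies 24 months of accrual. With one HIV-uninfected partner per couple, 200 is the planned average number of PrEP users per clinic.

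**2. Between-clinic comparison.** Inputs: m persons per clinic (200 from Sample size; 20 as an illustration for sparsely sampled outcomes), two-sided alpha 0.05 (Sample size), and an assumed ICC.

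Design effect: DE = 1 + (m − 1) × ICC.
True type I error of the unadjusted test: 2 × [1 − Φ(1.96 / √DE)].

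Example: m = 200 and ICC = 0.01 give DE = 1 + 199 × 0.01 = 2.99, √DE = 1.729, 1.96 / 1.729 = 1.134, and a type I error of 0.257.

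| ICC (assumed) | DE, m = 200 | Type I error | DE, m = 20 | Type I error |
|---|---|---|---|---|
| 0.001 | 1.20 | 7.3% | 1.02 | 5.2% |
| 0.01 | 2.99 | 25.7% | 1.19 | 7.2% |
| 0.02 | 4.98 | 38.0% | 1.38 | 9.5% |
| 0.05 | 10.95 | 55.4% | 1.95 | 16.0% |

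Simulation with 24 clinics of 200 persons agrees for the t test: 25% at ICC 0.01 and 56% at 0.05. For the chi-square test, with the ICC set on the latent scale, it gives 19% and 48%.

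**3. Baseline versus implementation.** Step 2's formula does not apply, because each clinic contributes to both sides. This case was simulated: 24 clinics in 6 steps of four or 12 steps of two (the article says groups of two to four), equal numbers per period, about 200 persons per clinic in all, a constant clinic effect, **no** time trend, 3,000 runs. The plain t test rejected in about 11% of runs at ICC 0.01 and 28-31% at ICC 0.05. Any calendar trend would add bias to this.

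**4. Comparison within clinics.** If both groups are equally represented in every clinic (for example 50:50 by sex), the clinic effect cancels and the variance factor is 1 − ICC. The type I error is 2 × [1 − Φ(1.96 / √(1 − ICC))] = 4.9% at ICC 0.01 and 4.4% at 0.05, so the tests are very slightly conservative. If the group share varies between clinics (SD 0.15), the simulated t test gives 7% and 15%.

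**5. Does the remedy work?** A t test on the 24 clinic means, 12 against 12, had a simulated type I error of 5.3%, 4.7% and 5.0% at ICC 0.01, 0.05 and 0.10. The price is the true amount of information: the effective sample for a between-clinic contrast is 4,800 / 2.99 = 1,605 at ICC 0.01 and 4,800 / 10.95 = 438 at ICC 0.05.

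**The case against.** The strongest reply is that the sentence is generic. It names no comparison, follows directly on a sentence about descriptive summaries, and might be meant for clinic-level variables, for which an ordinary test across clinics does not have this fault. The only baseline-versus-implementation contrast that the section spells out is the number initiated, and there the mixed model handles both clinic and calendar time. The article is condensed, and an SAP may say more.

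Part of this stands. That the tests will be applied to person-level data is an inference. It is a reasonable one: the article collects such data in quantity, and these are the only inferential methods it names outside the primary model. The SAP argument does not remove the point. The article does not leave the method open; it names tests for detecting differences, and they assume independence in a trial with 24 clusters.

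The size is also open to challenge, and rightly. There is no ICC to anchor it, and 200 per clinic does not suit every outcome. The Evaluation of PrEP adherence section limits tenofovir sampling to at most 10% of visits. Staff knowledge is described as a test before and after training, with no staff numbers per clinic, so the 200-person figures should not be applied to either.

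A reader might also infer that false-positive differences would be passed on as best practice. The article does not support this. Under PrEP technical assistance, practices are shared through adviser visits and rapid-cycle reports, and the Qualitative data section identifies what went well by content analysis. Neither route runs through these p-values.

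**Conclusion.** The point holds for a defined set of analyses: person-level comparisons between groups that differ by clinic, region, step or period. For these, the named tests understate uncertainty by an amount that runs from slight (about 7% true error at ICC 0.001 with 200 per clinic) to severe (about 55% at ICC 0.05). Sparser outcomes and period contrasts lie in between. All these figures rest on assumed ICCs; the period figures also rest on assumed step patterns and no time trend.

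It would be tempting to say that every person-level p-value in the trial will be far too small. The documents do not support that: contrasts balanced within clinics are not inflated, and the article does not list the comparisons to be tested. The primary analysis of Reach has its own clinic and time-step effects and is unaffected. This is a fault in the stated secondary methods, worth correcting because it is clear and cheap to correct.

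**What to change.** In the Quantitative data section, restrict the plain t and chi-square tests to comparisons for which independence is defensible. Then add wording to this effect: person-level comparisons across clinics, regions, steps or periods will use mixed models or generalized estimating equations with clinic as the cluster and a small-sample correction for 24 clusters, or t tests on clinic-level summaries; any comparison of baseline with implementation will also include a calendar-period term.

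Contrasts within clinics need no change on grounds of inflated error. Naming the comparisons to be tested would make it plain which rule applies to each.

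The cost is a sentence or two of analysis text and slightly more analysis work; no new data are needed. Intervals for between-clinic and between-period differences will be wider, which reflects the information actually available.

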#### Qualitative data

Qualitative data will be used to interpret and explain the results of the various individual RE-AIM dimensions or patterns of results across dimensions and clinics. We will use an inductive, content analysis approach to analyze the qualitative data (i.e., technical assistance reports, individual and provider interviews, and observation reports) involving an iterative coding process and category construction using qualitative analysis software. The development and analysis of the qualitative research codebook will be guided by the domains and constructs defined in the CFIR [18, 32]. The CFIR will provide contextual information on factors important for the intervention’s acceptability, adoption, and maintenance, as well as quality and fidelity in implementation (Table 3). We will characterize facility-level innovations that improve process and what went well and what was challenging and why, thereby identifying options and contextually appropriate opportunities for efficiency. Qualitative analyses will identify and describe key themes and explore variation within themes. Descriptive content will be inductively assembled to form explanatory accounts.

**Table 3 Tab3:** Application of Consolidated Framework for Implementation Science Research to the Partners Scale Up Project

CFIR domains/definitions	Respective project-specific codes
1. Innovation characteristics	1. Oral prep for HIV prevention
Innovation Source: Perception of key stakeholders about whether the innovation is externally or internally developed	▪ Ownership of the PrEP program at: National, clinic, and provider level, e.g., provider perception of MOH/NASCOP work vs project.
Adaptability: The degree to which an innovation can be adapted, tailored, refined, or reinvented to meet local needs.	▪ Adaptations—clinic level: PrEP eligibility PrEP baseline lab requirements Visit schedules
Complexity Perceived difficulty of the innovation, reflected by duration, scope, radicalness, disruptiveness, centrality, and intricacy and number of steps required to implement.	▪ Perceived difficulty of delivering PrEP: Perceived ease/complexity of counseling and delivering PrEP: time, labs, steps; challenges counseling about counseling about viral suppression
2. Outer setting	2. External influence of prep implementation
External policy and incentives A broad construct that includes external strategies to spread innovations including policy and regulations (governmental or other central entity), external mandates, recommendations and guidelines, pay-for performance, collaborative, and public or benchmark reporting.	▪ External enablers and policy: MOH policy framework and guidance MOH tools MOH supervision County government involvement
Peer pressure Mimetic or competitive pressure to implement an innovation, typically because most or other key peer or competing organizations have already implemented or are in a bid for a competitive edge.	▪ Clinic-level peer pressure: Motivation/pride from being the first to implement PrEP
3. Inner setting	3. Clinic-level factors
Structural characteristics The social architecture, age, maturity, and size of an organization	▪ Infrastructure and staff: Patient volume, space, staffing
Relative priority Individuals’ shared perception of the importance of the implementation within the organization	▪ Clinic-level priority: Tension between PrEP implementation (healthy person) vs ART services at the clinic (sick person)
Leadership engagement Commitment, involvement, and accountability of leaders and managers with the implementation of the innovation.	▪ Leadership engagement: Facility/HIV clinic manager involvement in PrEP implementation
Access to knowledge and information	▪ Staff training: Adequacy of training, models of PrEP training
Available resources	
4. Characteristics of individuals	4. Health care provider factors
Knowledge and beliefs about the innovation Individuals’ attitudes toward and value placed on the innovation, as well as familiarity with facts, truths, and principles related to the innovation.	▪ Provider adoption and experience: Knowledge and attitudes about PrEP
Self-efficacy Individual belief in their own capabilities to execute courses of action to achieve implementation goals.	▪ Self-efficacy: Staff confidence in counseling and delivering PrEP, staff confidence in counseling about PrEP and condoms, confidence in viral undetectable=no transmission (u=u)
5. Process	5. Prep implementation process
Engaging Attracting and involving appropriate individuals in the implementation and use of the innovation through a combined strategy of social marketing, education, role modeling, training, and other similar activities.	▪ Demand creation strategies: Successful and unsuccessful demand creation strategies ▪ Retention strategies Successful and unsuccessful engagement/retention strategies ▪ Stakeholder engagement
Champions Individuals who dedicate themselves to supporting, and “driving through” an [implementation], overcoming indifference or resistance that the innovation may provoke in an organization	▪ PrEP champions: Types, roles, and how they have emerged, challenges, and how to harness champions
External change agents Individuals who are affiliated with an outside entity who formally influence or facilitate innovation decisions in a desirable direction.	▪ External change agents: Roles and impact of PrEP technical advisors, county/sub county AIDS and STI coordinators involvement, other implementing partners
Execution Carrying out or accomplishing the implementation according to plan	▪ Fidelity, clinic innovations, and adaptations—PrEP provision: Clinical encounter form completeness, same-day PrEP initiation, requirements for baseline creatinine and hepatitis B testing, assessment of acute HIV symptoms, PrEP visit frequency/schedule, quantity of PrEP dispensed, PrEP vs condom disconnect between providers and patients, demand creation, and retention strategies ▪ Demand creation strategies ▪ Opportunities for efficient PrEP delivery
Innovation participants Individuals served by the organization that participate in the innovation, e.g., patients in a prevention program in a hospital.	▪ Patient experiences: Confidence in health system, stigma of coming to an HIV clinic, facilitators and barriers to access to PrEP, benefits/challenges of integrating PrEP in IV clinics, confidence in stopping PrEP when HIV partner achieves viral suppression
Reflecting and evaluating Quantitative and qualitative feedback about the progress and quality of implementation accompanied with regular personal and team debriefing about progress and experience	▪ M & E activities: Best practices, role of technical assistance, rapid cycle analysis, adoption of PrEP delivery, quality improvement activities, M & E measures to assess progress

